# COMMENCE trial (Comparing hypOtherMic teMperaturEs duriNg hemiarCh surgEry): a randomized controlled trial of mild vs moderate hypothermia on patient outcomes in aortic hemiarch surgery with anterograde cerebral perfusion

**DOI:** 10.1186/s13063-019-3713-9

**Published:** 2019-12-09

**Keywords:** Aortic arch surgery/hemiarch repair, Hypothermic circulatory arrest, Mild hypothermia, Antegrade selective cerebral perfusion, Cerebral protection, Stroke, Acute kidney injury, Prospective study, Randomized controlled trial

## Abstract

**Background:**

Aortic arch surgery remains the only viable life-saving treatment for aortic arch disease. However, the necessity for cessation of systemic blood flow with hypothermic cardiac arrest carries substantial risk of morbidity and mortality, including poor neurological outcomes and kidney failure. While uncontrolled studies have suggested the safety of operating at warmer temperatures, significant variables remain un-investigated, supporting the need for a randomized clinical trial (RCT) to produce evidence-based guidelines for perfusion strategies in aortic surgery. This study proposes a multi-center RCT in order to compare outcomes of warmer hypothermic strategies during aortic hemiarch surgery on a composite endpoint of neurologic and acute kidney injury (AKI).

**Methods/design:**

This is a prospective multi-center, single-blind two-arm RCT comparing mild (32 °C) versus moderate (26 °C) hypothermic cardiac arrest in patients (*n* = 282) undergoing hemiarch surgery with antegrade cerebral perfusion (ACP). The primary endpoint is a composite of neurological injury (incidence of transient ischemic attack and/or stroke) and Kidney Disease Improving Global Outcomes (KDIGO) stage 1 or higher AKI. Secondary outcomes include death, cardiopulmonary bypass time, bleeding, transfusion rates, prolonged mechanical ventilation, myocardial infarction, length of stay, and quality of life measures.

Patients will undergo 1:1 block randomization to each treatment arm on day of surgery. Sequence of operation will be at the surgeon’s discretion with mandatory guidelines for temperature and ACP administration. Perioperative management will occur as per enrolling center standard of care. Neurocognitive function will be assessed for neurological injury using validated neurological screening tests: NIHSS, MOCA, BI, and MRS throughout patient follow-up. Diagnosis and classification of AKI will be based on rising creatinine values as per the KDIGO criteria. Study duration for each patient will be 60 ± 14 days.

**Discussion:**

It is hoped that performing hemiarch surgery using mild hypothermia (32 °C) and selective ACP will result in a 15% absolute risk reduction in the composite outcomes. The potential of this risk reduction will translate into improved patient outcomes, survival, and long-term financial savings to the health care system. In addition, the results of this trial will be used to create the first-ever guidelines for temperature management strategy during aortic surgery.

**Trial registration:**

This trial is registered on ClinicalTrials.gov with the registration number NCT02860364. Registration date August 9th, 2016.

## Background

Thoracic aortic disease (TAD) is a silent epidemic affecting 15,000 people per year, with up to 45,000 deaths per annum in the United States, making it one of the leading causes of death in people over 65 [1]. New studies have shown an increased prevalence and incidence of TAD, with surgery remaining the only viable life-saving treatment [2, 3]. However, the way in which these surgeries must be conducted carries substantial risk of morbidity and mortality.

When surgery on the aortic arch is required, the necessity of stopping systemic blood flow to provide a clear operative field places perfusion-sensitive organs, such as the brain and kidneys, at significant risk of ischemic injury. Surgery on the aortic arch was only made possible in the mid-1970s, with the introduction of deep hypothermic cardiac arrest (DHCA) by Griepp et al. [4]. The concept of deep hypothermia to reduce oxygen and metabolic requirements of hypoxic tissue is well documented [5, 6], but it is not achieved without its own adverse effects on body homeostasis and processes, including longer cardiopulmonary bypass (CPB) times, increased coagulopathy, multi-organ dysfunction, systemic inflammatory response (SIRS), endothelial dysfunction, and neuronal apoptosis [7–11]. Unfortunately, these drawbacks are intimately associated with worse neurologic (transient ischemic attack (TIA) and stroke) and renal outcomes, which often result in debilitating and lifelong illnesses for patients.

Strokes post-cardiac surgery have been shown to double the duration and costs of hospitalization, and are associated with a five- to tenfold increase in early mortality, while up to 69% of survivors suffer severe physical disability, often requiring continuing care, rehabilitation, or placement in long-term care facilities [12]. Similarly, postoperative kidney injury can result in the need for permanent dialysis, requiring on-going hospital visits and substantial increases in mortality and morbidity [13]. These postoperative complications result in significant added expenditures for the health care system. It has been estimated that the economic impact of stroke post-coronary revascularization (which carries a substantially lower risk of stroke than aortic surgery) exceeds $2 to $4 billion dollars annually worldwide [14]. Thus, it can be inferred that stroke would have a similar, if not higher, economic impact among patients undergoing aortic arch surgery.

To mitigate neurological complications, Bachet and Kazui [15, 16] developed selective anterograde cerebral perfusion (sACP). By directly cannulating the axillary or innominate artery, uninterrupted physiologic cerebral perfusion to the brain could now be maintained in patients during periods of circulatory arrest. This afforded patients almost complete neurological protection during arch surgery, effectively changing total body hypothermic circulatory arrest to isolated lower body circulatory arrest. Despite these advances in surgical technique, these procedures still carry high mortality and morbidity risks, and may be related to the adverse effects of profound hypothermia [17]. In an attempt to negate these risks, a trend towards significantly warmer core body temperatures has emerged across cardiac centers with positive outcomes being observed [8, 12, 13].

Previous retrospective studies and large meta-analyses comparing deep (14.1–20 °C) and moderate (20.1–28 °C) hypothermic cardiac arrest (MHCA) during aortic arch surgery (with sACP) have shown no differences in hospital mortality, visceral organ protection, and neurologic outcomes [8, 18, 19]. It is believed that by performing these operations at even warmer temperatures (mild hypothermia, 28.1–34 °C) the aforementioned risks associated with DHCA and MHCA can be further mitigated. Multiple case studies examining outcomes post-aortic surgery with mild hypothermia have also revealed no significant differences in mortality, renal failure, and neurological injury; even showing benefits with reduced coagulopathies and in some studies decreased permanent neurological deficits [5, 8, 20, 21].

While retrospective and uncontrolled studies are numerous and suggest the safety of warmer arch surgery [8, 17, 18], there is significant parametric variability in these studies. The optimal temperature for hypothermic circulatory arrest remains unclear and is confounded by numerous variables that are also without consensus, including site of temperature monitoring, sACP cannulation site, sACP perfusion rates, rapidity of cooling/rewarming, and the determination of outcome data [5]. Furthermore, few studies directly compare outcomes of one strategy versus another, and no prospective randomized controlled trials (RCT) exist to guide such therapy [5, 20].

This lack of evidence-based medicine has resulted in significant practice variation, with no existing guidelines for optimal perfusion strategies in aortic arch surgery. Currently, the University of Ottawa Heart Institute (OHI) performs hemiarch surgery under mild hypothermic (32 ± 2 °C) circulatory arrest and unilateral sACP (uSACP). Pilot data from our mild hypothermic patients have demonstrated excellent outcomes with lower morbidity (combined stroke, need for dialysis, and deep sternal wound infection) and decreased needs for blood products when compared to patients operated under DHCA [22]. With positive and reproducible evidence supporting mild hypothermia, there is an urgent need for a RCT to address the aforementioned questions, reduce practice variability, and produce evidence-based guidelines for perfusion strategies in aortic surgery. Thus, the purpose of this RCT is to compare clinical outcomes between patients undergoing hemiarch surgery with ACP under mild hypothermic (32 ± 1 °C) circulatory arrest versus moderate hypothermic (26 ± 1 °C) circulatory arrest.

## Methods/design

### Study hypothesis

The aim of this study is to demonstrate that circulatory arrest using mild hypothermia (32 ± 1 °C) and uSACP will result in a 15% absolute risk reduction (from 35% to 20%) — in our composite outcome of neurologic and acute kidney injury (see definition below) during aortic hemiarch surgery, when compared to moderate hypothermia (26 ± 1 °C) and uSACP.

### Study design

This trial is a prospective multi-center, single-blind two-arm RCT comparing mild versus moderate hypothermia for circulatory arrest in hemiarch surgery on a composite outcome of neurological and acute kidney injury (AKI) in 282 patients undergoing aortic hemiarch surgery with uSACP. Consenting adult patients (≥ 18 years of age) undergoing ascending aorta and hemi-arch replacement with uSACP and an anticipated circulatory arrest time of less than 20 min will be randomized 1:1 to moderate hypothermia (26 ± 1 °C, Control group) versus mild hypothermia (32 ± 1 °C, Treatment group).

### Study setting

The principal study site for this RCT will be the University of Ottawa Heart Institute (UOHI), which is a quaternary care cardiovascular center with a large thoracic aortic program, performing over 200 thoracic aortic operations per year. Other participating sites in Canada include the Foothills Medical Centre (University of Calgary), London Health Sciences Centre (Western University), and Quebec Heart and Lung Institute (University of Laval).

### Study description

#### Eligibility criteria

##### Inclusion criteria

Age ≥ 18 yearsPlanned unilateral or bilateral selective anterograde cerebral perfusionAnticipated lower body arrest time of < 20 minAble to provide written informed consent

##### Exclusion criteria

Surgery for aortic dissection or urgent/emergent operationsTotal arch replacementInability to perform unilateral selective anterograde cerebral perfusion (severe axillary or innominate artery atherosclerosis/stenosis)Patients with known/documented coagulopathiesPatients with cold agglutinin disease or those that test positive on routine preoperative screeningPre-existing severe neurological impairment or inability to accurately assess neurocognitive function as determined by the operating surgeonSevere carotid disease
Any patient with previously documented carotid stenosis of ≥ 70% (via Doppler ultrasound, magnetic resonance angiography, or computer tomography angiography) without neurological deficitsCarotid stenosis ≥ 50% with neurological deficitsPrevious carotid endarterectomy or stentingPatients in renal failure or currently being treated with renal replacement therapy (RRT) or estimated glomerular filtration rate (eGFR) < 30 ml/min/1.73m^2^Use of an investigational drug or device at time of enrollmentParticipation in another clinical trial which interferes with performance of this study’s procedures or assessment of outcomes

#### Enrollment

Screening will occur at the time of the initial appointment, at which time patients will be seen and assessed by the cardiac surgeon for consideration of aortic arch surgery. Patients who are booked for aortic hemiarch surgery with planned hypothermic circulatory arrest and ACP will be assessed for the aforementioned eligibility in the clinical trial. Once deemed eligible and written informed consent obtained, baseline neurological screening will be performed by trained personnel.

The following baseline information will then be collected at either this initial visit, or at the time of the preoperative anesthesia clinic visit (see SPIRIT Fig. 1):
Clinical information
Demographics—age, sexHTN (hypertension)DM (diabetes)DLP (dyslipidemia)NYHA class (New York Heart Association)Aortic stenosis
i.Graded: mild, moderate, severeAortic valve regurgitation
i.Graded: 1 to 4+CCS class (Canadian Cardiovascular Society)CAD (coronary artery disease)Previous history of strokePrevious history of TIA (transient ischemic attack)Carotid stenosisRenal diseasePVD (peripheral vascular disease)COPD (chronic obstructive pulmonary disease)Pulmonary HTNSmoking historyETOH use (ethanol)Congenital aortic diseaseAortic diameterEuroscore IIPhysical examination
Height (cm)Weight (kg)BMI (kg/m^2^)—body mass indexBSA (m^2^)—body surface areaLaboratory tests/investigations
Hb (g/L)—hemoglobinPlt (× 10^9^/L)—plateletINR (international normalized ratio)Cr (umol/L)—creatinineBUN (mmol/L)—blood urea nitrogeneGFR (ml/min/1.73m^2^)—estimated glomerular filtration rateHbA1C (%)—hemoglobin A1cNeurocognitive testing
NIHSS (The National Institutes of Health Stroke Scale)MOCA (Montreal Cognitive Assessment)MRS (Modified Rankin Scale)—only postoperatively in event of strokeBI (Barthel Index)Quality of life
SF-12 (Short Form) survey

**Fig. 1 Fig1:**
[figure not shown]
SPIRIT Figure: Summary of patient study visits and assessments. Abbreviations: POD – Postoperative Day, NIHSS – The National Institutes of Health Stroke Scale, MOCA - The Montreal Cognitive Assessment, MRS – Modified Rankin Scale, BI - Barthel Index, CAM – Confusion Assessment Method, SF-12 – Short Form Survey, DW-MRI – Diffusion-Weighted Magnetic Resonance Imaging, CT – Computer Tomography. * When clinically indicated – based on a physician assessment of the patient symptoms. ** Or prior to discharge

#### Randomization

Once study eligibility, consent, and baseline assessment are completed, subjects will be randomized using a web-based randomization tool (DACIMA 3.3.8) [23] in a 1:1 ratio on the day of surgery to either mild or moderate hypothermia strategies during aortic hemiarch surgery with uSACP. Block randomization to each treatment arm will be used across participating centres.

In order to ensure a normal distribution of kidney function among patients in both treatment arms, stratified randomization will be performed based on two eGFR ranges: 30–59 ml/min/1.73m^2^ and ≥ 60 ml/min/1.73m^2^ [24]. Randomization will also be stratified by site to reduce possible confounding from differences in standard of care practices across sites.

#### Study intervention

Subjects will be randomly allocated to one of the following two arms:
Mild hypothermia (32 ± 1 °C) strategy for circulatory arrest (intervention group)Moderate hypothermia (26 ± 1 °C) strategy for circulatory arrest (control group)

#### Conduct of aortic hemiarch surgery and hypothermic strategy

Sequence of operation up until circulatory arrest with CPB will be at the surgeon’s discretion. All surgical procedures will be performed via median sternotomy (or upper hemi-sternotomy). During the aortic arch anastomosis, continuous, unilateral selective ACP using axillary or innominate artery cannulation will be employed. Unilateral SACP may be converted to bilateral ACP at the surgeon’s discretion if adequate cerebral flows are not achieved or if there are concerns with cerebral oximetry measurements.

Once on CPB, the patient will be cooled to a nasopharyngeal (NP) temperature of either 32 °C or 26 °C, depending on to which treatment arm the patient has been randomized. Bladder temperature and venous blood temperature will both be monitored as additional temperature sites. Unilateral SACP will only be initiated once the target temperature has been reached. ACP via the axillary or innominate artery will be commenced with target flows of 10–15 ml/kg/min with temperatures of 32 °C or 26 °C. ACP flows will be titrated to a right radial blood pressure (BP) of 60–70 mmHg. Heater/cooler temperatures are not to exceed 37.5 °C and a temperature gradient of less than 10 °C should be maintained at all times.

After completion of the aortic hemiarch replacement, CPB will be resumed and the patient re-warmed to 35 °C prior to coming off CPB, with a ≤ 1 °C temperature difference between temperature monitoring sites (NP and bladder probes).

#### Transfusion strategy

Transfusion triggers (for packed red blood cells only) will be adhered to whenever possible without compromising patient safety or center-specific transfusion protocols. Thus, a liberal transfusion threshold of Hb < 95 g/L will be used intraoperatively and in the intensive care unit (ICU), while a Hb < 85 g/L will be adhered to after transfer to the ward. These values were chosen based on the TRICS-III trial (Transfusion requirements in Cardiac Surgery III) and will be used for the duration of the patients hospital stay [25].

#### Frequency and duration of follow-up

Study participants will be followed up daily during their postoperative course in hospital, including the ICU. Intraoperative information will be collected from the anesthetic record, surgical notes, and perfusion records. Intraoperative data collection will include total operative time (skin to skin time), total CPB time, total cross-clamp time, total hypothermic cardiac arrest time, uSACP time, cooling time, re-warming time, nadir nasopharyngeal and bladder temperature, mean arterial systolic and diastolic BP, nadir hemoglobin concentration (g/L), nadir hematocrit (%), intraoperative red blood cell (RBC) transfusion (units), and highest dose/agent used for intraoperative inotrope or vasopressor support.

Postoperative data will include tabulations from the following areas:
Mortality
Death from any causeUp to POD 60 ± 14Neurological injury
TIAStrokeNIHSS—POD 2 ± 2, 6 ± 1 (or prior to discharge), and 60 ± 14MOCA—POD 2 ± 2, 6 ± 1 (or prior to discharge), and 60 ± 14MRS—only in event of postoperative strokeBI—only in event of postoperative strokeDelirium
Assessed and scored as per the Confusion Assessment Model (CAM)—POD 2 ± 2 and 6 **±** 1Acute kidney injury
Creatinine and BUN—POD 0, 1, 2 ± 2, 4 ± 1, 6 ± 1 (or prior to discharge), and 60 ± 14Urine output—up to 48 hRenal replacement therapy (dialysis)Prolonged mechanical ventilation
Mechanical ventilation times ≥ 48 hMeasured in hours from time of admission to the ICUCoagulopathy
Mediastinal re-exploration for bleeding or tamponadeChest tube outputsPerioperative transfusions
Packed red blood cells (pRBCs)PlateletsFresh frozen platelets (FFP)CryoprecipitatePostoperative myocardial infarction
Electrocardiogram (ECG)TroponinsInotropic support longer than 48 h
Agent (amiodarone, epinephrine, norepinephrine, dopamine, dobutamine, milrinone, vasopressin) and dose (mcg/kg/min)Length of stay
ICU daysTotal hospital daysQuality of life measures
SF-12—POD 60 ± 14

#### Postoperative assessment and follow-up study visits

On postoperative days 2 ± 2 days, 6 ± 1 days, and 60 ± 14 patients, will undergo neurocognitive screening by trained personnel. NIHSS and MOCA examinations will be made at each time point (or prior to discharge for time point 6 ± 1 days). In the event a neurological deficit is identified during assessment and/or based on patient symptoms (focal/global, motor/sensory loss, or prolonged delirium/agitation), neurological imaging will be obtained using computed tomography (CT) head or diffusion-weight magnetic resonance imaging (DW-MRI). MRIs will be used only if symptom onset is acute in nature requiring rapid diagnosis. Patients will also undergo MRS assessment only in the event of a postoperative stroke. BI scoring will be performed preoperatively and postoperatively only in the event of a stroke. Quality of life measures will be assessed using SF-12 health survey and obtained preoperatively and at final follow-up at 60 ± 14 days (see SPIRIT Fig. 1).

#### Primary outcome and definitions

The primary efficacy endpoint for this study will be a composite of neurologic injury and AKI that occurs at any time over the 60 ± 14 day study period. Definitions are defined in secondary outcomes below.

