i.Scores > 26—no cognitive impairment (normal exam)ii.Scores < 26—mild cognitive impairmente.Modified Rankin Scale (MRS)—only to be used in the event of a postoperative stroke. The MRS is a reliable and reproducible scoring method for the assessment of deficits post-stroke in patients. Scores range from 0 to 6 [32, 33]
i.0, no symptomsii.1, no significant disability: able to carry out all usual activities, despite some symptomsiii.2, slight disability: able to look after own affairs without assistance, but unable to carry out all previous activitiesiv.3, moderate disability: requires some help, but able to walk unassisted.v.4, moderately severe disability: unable to attend to own bodily needs without assistance, and unable to walk unassistedvi.5, severe disability: requires constant nursing care and attention, bedridden, incontinentvii.6, deadf.Barthel Index of Activities of Daily Living (BI)—the BI is formed by several disability indexes and is a reliable and reproducible scoring method for the assessment of activities of daily living (ADLs) post-stroke in patients. Scores range from 0 to 20 [34–36]
i.Lower scores indicate increased disabilityii.When used to measure improvement after rehabilitation, changes of more than two points in the total score reflect probable genuine changeiii.Change on one item from fully dependent to independent are also likely to be genuine
2.Incidence of acute kidney injury (AKI)
Postoperative AKI will be assessed using the KDIGO criteria [37–39] and are summarized in Table 1Creatinine measurements will serve as the main indicator for assessing AKIAll those with KDIGO stage 1 or higher AKI will be considered to have sustained postoperative AKICreatinine measurements will be performed with routine bloodwork on POD 0, 1, 2 ± 2, 4 ± 1, 6 ± 1, and 60 ± 14 daysUrine output for the diagnosis of AKI will only be measured in the immediate postoperative period (48 h)Blood urea nitrogen (BUN) levels will also be obtained on the same days

**Table 1 Tab1:** KDIGO classification of AKI

Stage	Serum creatinine	Urine output
1	1.5–1.9 times baseline or ≥ 0.3 mg/dl (26.5 μmol/l) increase	< 0.5 ml/kg/h for 6–12 h
2	2.0–2.9 times baseline	< 0.5 ml/kg/h for ≥12 h
3	3.0 times baseline or Increase in serum creatinine to ≥ 4 mg/dl (353.6 μmol/l) or initiation of renal replacement therapy	< 0.3 ml/kg/hr. for ≥24 h or Anuria for ≥ 12 h3.Incidence of delirium
Delirium—reversible postoperative delirium lasting more than 48 h without localizing signs

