This RCT will use the newer KDIGO criteria for assessing AKI, which identifies significantly more AKI in patients than both the Risk, Injury, Failure, Loss of kidney function, and End-stage kidney disease (RIFLE) and AKIN criteria [38, 45]. Specifically, KDIGO criteria have been shown to have a greater sensitivity in diagnosing AKI when compared to RIFLE and AKIN (51% versus 46.9% for RIFLE, *p* <  0.01 and 38.4% for AKIN, *p* <  0.001) [45]. It is also expected that the incidence of AKI will be higher in this study based on the type of surgery being performed, which necessitates a period of lower body ischemia time. Thus, we hypothesize a 25% incidence of KDIGO stage 1 AKI for this trial.

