#### Sample size

Taking into consideration the aforementioned incidence rates of both neurologic injury and AKI, a composite outcome of ~ 35% should represent the incidence of these injuries in patients undergoing hemiarch surgery using traditional methods of hypothermia. This accounts for a 5–10% overlap that will likely exist, where a patient will suffer both types of injuries.

We hypothesize that circulatory arrest using mild hypothermia (32 °C) and uSACP during aortic hemiarch surgery will result in a 15% absolute risk reduction in composite outcomes (neurologic injury and AKI) from 35% to 20%. With an alpha (type 1 error) of 0.05 and power of 80%, and a 5% loss to follow-up, approximately 141 subjects will be needed in each group for a total of a 282 patients.

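### The AKI part of the primary endpoint has no perioperative limit, so a single raised creatinine at the two-month visit counts as postoperative AKI

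*Protocol article*

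**What the plan says.** Under Primary outcome and definitions, the endpoint is a "composite of neurologic injury and AKI that occurs at any time over the 60 ± 14 day study period", and the reader is sent to the secondary outcomes for the definitions.

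The AKI item there makes creatinine the main indicator and counts every patient at KDIGO stage 1 or above. Creatinine is taken "with routine bloodwork on POD 0, 1, 2 ± 2, 4 ± 1, 6 ± 1, and 60 ± 14". The list under Frequency and duration of follow-up repeats this schedule under the AKI heading. In Table 1 the stage 1 creatinine criterion is "1.5–1.9 times baseline or ≥ 0.3 mg/dl (26.5 μmol/l) increase", with no period for the rise and no confirmatory value.

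Other items do carry limits: urine output for AKI is confined to 48 h, and transfusions are counted to POD 7 or discharge.

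On planning, Statistical consideration says "Thus, we hypothesize a 25% incidence of KDIGO stage 1 AKI for this trial". The Sample size section takes composite rates of 35% (moderate) and 20% (mild), 80% power, a 0.05 type 1 error and 5% dropout, and concludes that "approximately 141 subjects will be needed in each group for a total of a 282 patients".

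**The concern.** The intervention takes place only during the operation, and the component is meant to capture acute kidney injury that follows it. The rule as printed also captures any creatinine difference present two months later, whatever its cause: a change of medication, an intercurrent illness or slow drift. The visit windows leave a gap from about day 7 (POD 6 + 1) to day 46 (POD 60 − 14) with no scheduled creatinine, so a first rise seen at the last visit cannot be dated or shown to be acute.

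Two things are at stake. One is meaning: the endpoint would label as postoperative AKI something the schedule cannot identify as such. The other is power: events that temperature does not influence add to both arms and shrink the difference the trial is sized to detect.

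**Working it through.** **Inputs from the protocol article.** Composite 35% vs 20%; alpha 0.05 (sidedness not stated, two-sided assumed); power 80%; 5% loss; 141 per group; 1:1 allocation; chi-squared test on the binary composite. Evaluable per arm: 141 × 0.95 = 133.95, taken as 134.

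**Assumed input.** q is the share of otherwise event-free patients who meet stage 1 only on the day-60 creatinine. The documents give no figure, so a range of 1% to 10% is shown.

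**The plan's own figure.** With unpooled variance, n = (1.960 + 0.842)² × (0.35 × 0.65 + 0.20 × 0.80) / 0.15² = 7.849 × 0.3875 / 0.0225 = 135.2, so 136. Then 136 / 0.95 = 143.2, so 144 per arm. The stated 141 is described as approximate and lies within 3% of this. The sample size is not in error.

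**Power formula (pooled two-proportion test).** Power = Φ{[d√n − 1.960 √(2p̄(1 − p̄))] / √(p₁(1 − p₁) + p₂(1 − p₂))}, where d = p₁ − p₂ and p̄ is the mean of p₁ and p₂. At 35% vs 20% and n = 134: (1.736 − 1.238) / 0.622 = 0.801, so power is 78.8% (80.9% at 141).

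**Late rises unrelated to arm.** Each rate becomes p + (1 − p)q, so the arms are 0.35 + 0.65q and 0.20 + 0.80q, and the difference is 0.15(1 − q). The mild arm has more event-free patients and so collects more late events. At q = 5% that is 134 × 0.80 × 0.05 = 5.4, against 134 × 0.65 × 0.05 = 4.4.

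| q | Moderate | Mild | Difference (points) | Power, 134/arm | Evaluable/arm for 80% |
|---|---|---|---|---|---|
| 0 | 35.0% | 20.0% | 15.0 | 78.8% | 138 |
| 1% | 35.7% | 20.8% | 14.9 | 77.4% | 144 |
| 2% | 36.3% | 21.6% | 14.7 | 75.9% | 149 |
| 5% | 38.3% | 24.0% | 14.3 | 71.4% | 165 |
| 10% | 41.5% | 28.0% | 13.5 | 64.2% | 195 |

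**Late rises that temperature does affect.** Let the late-only share be q in the moderate arm and q × RR in the mild arm. At n = 134:

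| Late RR | q = 2% | q = 5% | q = 10% |
|---|---|---|---|
| 1.00 | 75.9% | 71.4% | 64.2% |
| 0.70 | 78.8% | 78.7% | 79.0% |
| 0.57 (the planned overall RR) | 79.9% | 81.6% | 84.2% |

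The loss is therefore conditional. It is full when late rises are independent of arm, vanishes near RR 0.70, and becomes a small gain at the planned RR.

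**The case against.** The best reply is that the article adopts the KDIGO criteria by citation and only summarizes them in Table 1. Any time limit in those criteria would then govern, and the phrase about any time would say only when an AKI may occur. The full protocol and a later SAP may also be more precise. Part of this stands: the article does not show that the sponsor intends to score a late drift as AKI. But no limit on the rise is printed anywhere in it, the one window it states for the component runs to day 60 ± 14, and the day-60 creatinine is listed as an AKI measurement. That is a stated rule, not a detail left out.

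It can also be said that q is unknown, that the 35% and 20% are not stated to exclude late events, and that the direction of the effect on power depends on whether temperature influences late rises. All of this stands and limits how firmly a loss can be claimed. In partial answer, the 25% AKI rate is built from AKI reported after cardiac surgery, raised for KDIGO sensitivity and lower body ischemia, with no mention of late rises.

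A reader might further infer that the endpoint becomes dependent on attendance at day 60. A late-only creatinine event does need that visit, but so does the final neurologic assessment, which should stay; expected loss is about 5%, and nothing suggests that it differs by arm. A reader might also infer that all renal events after the first week should be dropped. The documents do not support that either: Table 1 counts initiation of renal replacement therapy as stage 3, and permanent dialysis is among the harms that motivate the trial.

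**Conclusion.** The point holds as a defect in the endpoint rule, of moderate severity. As written, one two-month creatinine 26.5 μmol/l above baseline counts as postoperative AKI in the primary endpoint, and the schedule cannot show that it was acute or operative.

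The cost in power is conditional. If late-only rises are unrelated to arm, it is about 1.4 points at q = 1% (78.8 − 77.4), 2.9 at 2%, 7.4 at 5% and 14.6 at 10%. It is less or nil if temperature also affects them. That the effect will be diluted, or that power will in fact drop to some 64%, goes beyond the documents: the first needs independence from arm, the second also needs one in ten event-free patients to score only at the late visit. Events added independently of arm cost power and do not inflate the type I error.

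**What to change.** Before any unblinded analysis:

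- State which creatinine is the reference value.
- Restrict the creatinine-based AKI criterion of the primary endpoint to a stated perioperative window covered by the POD 0 to 6 ± 1 measurements, and write the period of the rise into Table 1. The exact window is the sponsor's to set.
- Keep initiation of renal replacement therapy, and stroke/TIA, in the primary endpoint to day 60 ± 14.
- Report the day-60 creatinine/eGFR as a separate secondary renal outcome, adjusted for baseline.
- Give the any-time definition as a sensitivity analysis.

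The measurements are already scheduled, so no new data are needed. The costs are that a few late creatinine-only events leave the primary endpoint, and that changing the endpoint wording of a recruiting trial needs a documented amendment. Statistical analysis says the SAP will be written only once data collection is complete, so settling the rule now also avoids a late choice about which creatinines count.
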